## Abstract

**Introduction:** Septic shock in children still carries substantial mortality and morbidity. While resuscitation with 40–60 mL/kg intravenous fluid boluses remains a cornerstone of initial resuscitation, an increasing body of evidence indicates potential for harm related to high volume fluid administration. We hypothesize that a protocol on early use of inotropes in children with septic shock is feasible and will lead to less fluid bolus use compared to standard fluid resuscitation. Here, we describe the protocol of the Early Resuscitation in Paediatric Sepsis Using Inotropes – A Randomised Controlled Pilot Study in the Emergency Department (RESPOND ED).

**Methods and analysis:** The RESPOND ED study is an open label randomised controlled, two arm, multicentre pilot study conducted at four specialised paediatric Emergency Departments. Forty children aged between 28 days and 18 years treated for presumed septic shock will be randomized in a 1:1 ratio to early inotropes vs. standard fluid resuscitation. Early inotrope treatment is defined as the commencement of a continuous intravenous adrenaline infusion after 20 mL/kg fluid bolus resuscitation. Standard fluid resuscitation is defined as delivery of 40 to 60 mL/kg fluid bolus resuscitation prior to commencement of inotropes. In addition to feasibility outcomes, survival free of organ dysfunction censored at 28 days will be assessed as the main clinical outcome. The study cohort will be followed up at 28 days, and at 6 months post enrolment to assess quality of life and functional status. Biobanking nested in the study cohort will be performed to enable ancillary biomarker studies.

**Ethics and dissemination:** The trial has ethical clearance (Children's Health Queensland, Brisbane, HREC/18/QCHQ/49168) and is registered in the Australian New Zealand Clinical Trials Registry (ACTRN12619000828123). Enrolment commenced on July 21st, 2019. The primary manuscript will be submitted for publication in a peer-reviewed journal.

**Trial Registration:** Australian and New Zealand Clinical Trials Registry, ACTRN12619000828123.

## Introduction

Sepsis, characterised by infection with associated organ dysfunction (1, 2), represents one of the leading acutely life-threatening conditions in pediatric Emergency Departments (ED) (3). The burden of sepsis on child health extends beyond mortality (4, 5) to morbidity and long-term sequelae which may dramatically affect Quality of Life (QoL) after discharge (6, 7). Improving recognition and treatment of sepsis is a priority for the World Health Organisation (8), and regional initiatives to improve the treatment of children with sepsis are underway in several countries (9, 10). Currently, best practice comprises timely delivery of a bundle consisting of intravenous antibiotics, blood culture and lactate sampling, and intravenous fluid boluses (11). Improved risk-adjusted survival rates have been shown for children treated with a sepsis bundle within 1 h of sepsis recognition (12).

Recent recommendations for treatment of sepsis and septic shock in children include the American College of Critical Care Medicine clinical practice parameters (13), and the 2020 paediatric Surviving Sepsis Campaign (SSC) guidelines (11). While both advocate for the administration of 40–60 mL/kg of fluid bolus therapy prior to the commencement of intravenous inotropes, the 2020 SSC added caution for fluid bolus therapy if intensive care resources are unavailable given the evidence towards worse survival in children with severe infections observed in the Fluid Expansion as Supportive Therapy (FEAST) study (14). The aim of administering fluid boluses in paediatric septic shock is to restore haemodynamic function and support the cardiovascular system, ensuring adequate perfusion to organs via clinical endpoints such as normalisation of heart rate, blood pressure and capillary refill. An increasing body of observational studies suggests potential harm related to excessive fluid delivery, including prolonged ventilation, increased mortality and ICU length of stay (15). Emergency and intensive care physicians report ongoing high fluid use in sepsis, and a high variability exists in local practices (16, 17). The premise for use of intravenous inotropes stems from observational data indicating that children with septic shock frequently manifest myocardial dysfunction coupled with variable degrees of vasoplegia which may benefit from catecholamines such as adrenaline (18). To date, there are limited high-quality randomised-controlled trials (RCTs) investigating optimal resuscitation therapies for children with septic shock. The timing and amount of fluids administered remain one of the most controversial topics in sepsis resuscitation (19).

For this purpose, we designed the Early Resuscitation in Paediatric Sepsis Using Inotropes – A Randomised Controlled Pilot Study in the Emergency Department (RESPOND ED). This pragmatic pilot study tests the feasibility of a paediatric parallel group RCT comparing early inotropes vs. standard fluid resuscitation in children aged between 28 days and 18 years presenting with suspected septic shock. We hypothesized that a protocolised early commencement of intravenous inotropes is feasible and that early inotropes will reduce the volume of resuscitation fluids administered compared to standard sepsis resuscitation. Here, we describe the RESPOND ED study protocol and statistical analysis plan.

## Methods

### Study Design and Setting

The RESPOND ED study is a pilot multicentre, open label, pragmatic randomized controlled trial (RCT) for children aged between 28 days and 18 years treated for septic shock (Figure 1). The study will recruit across four tertiary Emergency Departments (ED) and Paediatric Intensive Care Units (PICU) of participating sites in Queensland, Australia. The trial compares***early inotropes*** defined as adrenaline infusion started after 20 mL/kg fluid resuscitation, with ***standard care*** defined as providing up to 40–60 mL/kg fluid resuscitation prior to initiation of inotropes (11, 13). The study protocol has been approved by the Children's Health Queensland Hospital and Health Service Human Research Ethics Committee (HREC/18/QCHQ/49168) and registered with the Australian New Zealand Clinical Trials Registry (ACTRN12619000828123, June 2019). The trial abides by the Standard Protocol Items: Recommendations for Interventional Trials (SPIRIT) guidelines (20).

**Figure 1 F1:**
[figure not shown]
CONSORT participant flow diagram for RESPOND ED.

### Participants

#### Inclusion and Exclusion Criteria

Included will be children aged between 28 days and 18 years, where the treating clinician decides to treat for septic shock and administer intravenous antibiotics and an intravenous fluid bolus. Randomisation will occur after participants have received at least 20mL/kg fluid bolus in the last 4 h (or 1,000 mL fluid bolus in patients weighing over 50 kg), and the treating clinician must have decided to continue treating due to ongoing signs of shock. The exclusion criteria relate to patient characteristics which interfere with the study intervention and presence of chronic conditions which can interfere with the clinical outcome, as detailed in Table 1.

**Table 1 T1:** Inclusion and exclusion criteria.

**Rule**	**Criterium**	**Definition**
Inclusion	Age	• Aged ≥28 days and <18 years
	Illness	• Treated for sepsis
	Treatment	• Received at least 20 ml/kg fluid bolus in the last 4 h and clinician decides to continue treating signs of shock
	Consent	• Parental/caregiver consent prior to or after enrolment
Exclusion	Age	• Preterm babies born <34 weeks gestation that have a corrected age of <28 days
	Treatment	• Received ≥40 mL/kg of fluid boluses during the 4 h pre-enrolment • Inotrope infusion commenced pre-enrolment • Lack of access (intraosseous, central venous or peripheral) to administer fluids and/or inotropes after 60 min of enrolment
	Co-morbidities	• Cardiomyopathy or chronic cardiac failure • Chronic hypertension due to cardiovascular or renal disease, requiring regular antihypertensive treatment. • Known chronic renal failure (defined as requiring renal replacement therapy) • Known chronic hepatic failure • Palliative care patient/patient with limitation of treatment (not for inotropes, cardiopulmonary resuscitation, extracorporeal membrane oxygenation, intubation or ventilation)
	Illness severity	• Cardiopulmonary arrest in the past 2 h requiring cardiopulmonary resuscitation of >2 min duration, or death is deemed to be imminent or inevitable during this admission. • Major bleeding with haemorrhagic shock • Sepsis is not likely to be the cause of shock
	Previous study enrolment	• Enrolment in RESPOND study <6 months prior

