#### Screening and Consenting

Participants will predominantly be screened and recruited in the ED but can be recruited in PICU (Figure 1). Consent will be obtained from the guardians with the additional option to consent for biobanking. Where possible, prospective consent will be sought. Due to the emergency nature of septic shock, it is anticipated that in certain situations timely informed consent may not be feasible. In this circumstance a consent-to-continue approach will be applied [i.e., patients can be enrolled in the study if prospective consent cannot be obtained in a timely manner, but data can only be used in the analysis if the parents thereafter provide their written consent to continue in the study; also termed “deferred” or “delayed” consent (21)]. Informed consent will be sought from the parent/guardian by the study team or medical officer as soon as practical.

Screening will start at the time when the medical team decides to treat a patient for sepsis as per the institutional sepsis pathway (Queensland Paediatric Statewide Sepsis Pathway, which is being used at all study sites) to enable a pragmatic screening entry point. The trial does not mandate specific physiological thresholds to assess shock, rather the point of enrolment reflects the decision by the treating clinician to start a sepsis treatment bundle. Clinicians are advised to give a first fluid bolus of 20 mL/kg (or 1,000 mL fluid bolus in patients >50 kg) as per SSC guidelines irrespective of any decisions regarding enrolment in the study. Clinicians can give this amount of fluid as one bolus or split into aliquots of smaller amounts of bolus fluid.

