#### Standard Care

In the standard arm, patients will receive standard care as per site specific protocols based on international guidelines (11, 13). Specifically, patients in the standard arm will receive 40–60 mL/kg of fluid bolus therapy prior to initiating inotropes, thus, 20–40 mL/kg bolus fluid *after* randomisation (in addition to the 20 mL/kg bolus fluid, or 1,000 mL fluid bolus in patients >50 kg, which has to be administered to meet enrolment criteria). Further fluid and inotrope decisions in the standard care arm are at the discretion of the treating physician. The standard care is aligned with education provided at the study sites through the Paediatric Sepsis Pathway project (Queensland Sepsis collaborative) since 2018, which advocates for the administration of sepsis resuscitation bundles as per the Surviving Sepsis Campaign.

Patients who improve in <4 h can in principle be admitted to the ward as per local practice. In patients deteriorating despite 40–60 ml/kg fluid boluses, inotropes should be commenced, and the dose rate should be increased until stabilisation occurs. Admission to PICU with appropriate monitoring should be sought as per local practice.

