#### Analysis

Using the Consolidated Standards of Reporting Trials (CONSORT) flow chart (Figure 1) (20), we will describe the number of screened patients, those meeting inclusion and exclusion criteria, the number consented, and numbers of those who withdrew consent. In addition, we will provide in the text details of the consent process, including proportion of children with prospective consent vs. consent to continue, reasons why consent to continue was used, and time from enrolment to obtaining written consent in hours (IQR). Time from randomisation to initiation of allocated treatment will be reported. Descriptive statistics will be utilised to report on demographics, clinical history and baseline clinical characteristics of patient allocated to each of the study arms (Supplementary Table 1). Statistical comparison between the characteristics of the two arms at baseline will not be undertaken. The feasibility and clinical outcome measures (Supplementary Tables 2, 3) will be compared with the estimate of the difference and corresponding 95% confidence intervals (CIs). Continuous outcomes are assumed to be non-normally distributed, and as such quantile regression will be used to generate the CIs. A test of two proportions will be used for the binary outcomes. Analyses will be by intention-to-treat. Adverse events will be presented descriptively (Supplementary Table 4).

We will graphically compare physiological measures, heart rate, systolic blood pressure, pulse pressure (systolic minus diastolic blood pressure), shock index (heart rate divided by systolic blood pressure) and use of fluid bolus volume (in ml/kg) over time, using values measured during the first 24 h, comparing the intervention group to the control group, using values measured during the first 24 h.

We anticipate that <30% of RESPOND ED study patients will be co-enrolled into a concomitant study investigating metabolic resuscitation, named RESPOND PICU (ACTRN12619000829112) (27). Given that the study is a pilot feasibility study, analyses on RESPOND ED will occur separately from RESPOND PICU.

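### The access exclusion is timed 60 minutes after enrolment, so on the most natural reading it can be met after open-label allocation, which does not fit an unqualified intention-to-treat analysis

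*Protocol article*

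**What the plan says.** All references are to the protocol article.

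- **Access.** Table 1, under treatment exclusions, lists "Lack of access (intraosseous, central venous or peripheral) to administer fluids and/or inotropes after 60 min of enrolment". The two exclusions beside it look backwards: 40 mL/kg or more of bolus fluid in the preceding 4 h, and "Inotrope infusion commenced pre-enrolment".
- **Randomisation.** Inclusion and Exclusion Criteria: "Randomisation will occur after participants have received at least 20mL/kg fluid bolus in the last 4 h". Early Inotropes has adrenaline begin straight after randomisation. Blinding states that the trial is open label.
- **Enrolment, two meanings.** Standard Care describes the first 20 mL/kg as fluid "which has to be administered to meet enrolment criteria". Screening and Consenting says "the point of enrolment reflects the decision by the treating clinician to start a sepsis treatment bundle".
- **Consent.** Table 1 lists as an inclusion criterion "Parental/caregiver consent prior to or after enrolment". For children enrolled before consent, Screening and Consenting says "data can only be used in the analysis if the parents thereafter provide their written consent to continue in the study".
- **Analysis set.** Analysis: "Analyses will be by intention-to-treat". No exception is given for either group.

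**The concern.** An eligibility rule should be settled before allocation. A rule that can be met afterwards, by staff who know the arm, creates a way out of the randomised set, and intention-to-treat is meant to close such exits.

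The timing matters more than usual here because the main aim is feasibility, and time to inotropes and protocol violations are feasibility outcomes. A randomised child in whom the assigned treatment could not be given is an event the pilot exists to count. Table 1 instead classes that child as excluded.

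Consent raises a milder question. A randomised child whose parents do not later sign cannot be analysed, so the set is not strictly intention-to-treat, although the Analysis section calls it that.

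**Working it through.** **Step 1. When is enrolment?** The statements about it, side by side:

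| Place | What it implies |
|---|---|
| Standard Care | Enrolment follows the 20 mL/kg bolus, as randomisation does |
| Table 3 | Randomisation is an item within the enrolment phase |
| Study Outcomes; Tables 2 and 3 | The same 6-month visit is counted from randomisation in the text and from enrolment in the tables |
| Table 2; Data Collection | Fluid at 1, 4, 12 and 24 h is counted from enrolment in Table 2; Data Collection uses the same hours in a schedule that starts at randomisation |
| Table 1, neighbouring exclusions | A limit of 40 mL/kg before enrolment would have little content if enrolment came before the sepsis boluses |
| Screening and Consenting | Enrolment is the decision to start the sepsis bundle, hence before the bolus and before randomisation |

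Five entries point to enrolment at randomisation and one to an earlier point. On the majority reading, the 60-minute mark falls after allocation and after adrenaline is due to start. On the other reading it could fall before allocation, but nothing requires that it does.

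**Step 2. Does the rule conflict with the analysis statement?** On the majority reading, yes: a child can be randomised, meet an exclusion criterion, and still belong to an intention-to-treat set. The article does not say which statement prevails.

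**Step 3. Effect on the delivery-failure proportion, if such children were dropped.** The plan states no figure to reproduce on this point. Its only relevant number is N = 40 at 1:1, so 40/2 = 20 per arm and one child is 1/20 = 5% of an arm. The number of failures k is assumed. Intervals are exact (Clopper-Pearson) 95%.

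| k (assumed) | Kept: k/20 | 95% CI | Dropped: 0/(20 − k) | Upper 95% limit |
|---|---|---|---|---|
| 1 | 5% | 0.1 to 24.9% | 0/19 | 17.6% |
| 2 | 10% | 1.2 to 31.7% | 0/18 | 18.5% |
| 4 | 20% | 5.7 to 43.7% | 0/16 | 20.6% |

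When failures are dropped, the access-failure rate is 0% by construction, whatever the true rate.

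**Step 4. Effect on time to inotropes.** This is a simulation with assumed times. Delivered cases are lognormal with median 30 min and log-scale SD 0.5, capped at 60 min. Failures start at 60 min plus an exponential delay of mean 60 min. There are 20 children in the arm and 20,000 replicates.

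| k | Median, kept | Median, dropped | Mean, kept | Mean, dropped |
|---|---|---|---|---|
| 1 | 31.3 | 30.3 | 36.9 | 32.5 |
| 2 | 32.5 | 30.4 | 41.3 | 32.6 |
| 4 | 35.5 | 30.4 | 50.0 | 32.6 |

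The median shifts by 31.3 − 30.3 = 1.0, 32.5 − 30.4 = 2.1 and 35.5 − 30.4 = 5.1 min, in the direction that favours feasibility. The plan's threshold is a separation of at least 20 min, and it analyses continuous outcomes by quantile regression, so the median is the relevant column.

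**Step 5. Consent.** No inference is needed: data without later consent cannot be used. With an assumed loss of 5% to 20%, 40 randomised children leave 40 × 0.95 = 38 down to 40 × 0.80 = 32 analysed.

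**The case against.** The strongest reply is that the article never says a child who meets the access criterion after randomisation leaves the analysis. The unqualified intention-to-treat statement, read literally, keeps that child. This stands. A reader might infer from the heading *Exclusion* that the planned analysis removes these children, but the documents support only that the two statements are unreconciled.

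Second, Screening and Consenting places enrolment earlier, so the check might precede the envelope. This also stands as a possible reading. It moves part of the defect from the criterion to an undefined term.

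Third, failures would not be wholly hidden. Protocol violations are an outcome, deviations and their reasons are recorded, and the interval from randomisation to the start of assigned treatment is reported. This helps, unless excluded children drop out of those reports too.

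Fourth, a reader might infer that the rule acts mainly on the early-inotrope arm. The documents do not show this. The criterion covers fluids as well as inotropes by any route, and the standard arm also needs access for its further boluses after randomisation.

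Fifth, on consent, a reader might infer a concealed bias, for example that bereaved parents sign less often and that mortality is therefore understated. Nothing in the documents supports a rate or a direction. The restriction is stated openly under ethics approval, and consent rates are a feasibility outcome. The Analysis section promises numbers consented and withdrawn, and Data Quality and Monitoring already refers to patients both randomised and consented. What remains is a label.

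**Conclusion.** The point holds in limited form. On the reading that most of the article supports, Table 1 contains an exclusion that can be met after open-label allocation, and it is not reconciled with the intention-to-treat statement. If such children were dropped, the access-failure proportion would be zero by construction, against 5% to 20% for 1 to 4 failures in 20. The median time to inotropes would change by only about 1 to 5 min, so the damage would be to the count of delivery failures rather than to the 20-minute separation. The values of k, the simulated times and the consent losses are assumptions, because the documents give no such rates.

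The documents do not establish that these children will be removed, that adherence or separation will be overstated, or that clinical outcomes will be biased. The consent part is secondary: the analysis set needs an accurate name. Severity is moderate, and confidence is moderate because the timing rests on an inconsistently used term.

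**What to change.** 1. Define enrolment as a single time point, state its relation to opening the envelope, and use it throughout, including in Screening and Consenting.
2. Make access an eligibility check completed before the envelope is opened, and remove the 60-minute clause from the exclusions. Count children not randomised for this reason in the screening flow.
3. State that a child found to lack access after randomisation stays in the analysis as allocated, and report these children as non-delivery by arm.
4. Describe the analysis set as all randomised children with consent to use data, analysed as allocated. Report by arm the number randomised without such consent, after confirming that these counts fall within the ethics approval.

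The cost is one amended eligibility line, a definition, two sentences in the analysis section and extra rows in the flow diagram and feasibility table. Deviations and consent details are already recorded, so little new data collection is needed. The sample size does not change.

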#### Screening and Consenting

Participants will predominantly be screened and recruited in the ED but can be recruited in PICU (Figure 1). Consent will be obtained from the guardians with the additional option to consent for biobanking. Where possible, prospective consent will be sought. Due to the emergency nature of septic shock, it is anticipated that in certain situations timely informed consent may not be feasible. In this circumstance a consent-to-continue approach will be applied [i.e., patients can be enrolled in the study if prospective consent cannot be obtained in a timely manner, but data can only be used in the analysis if the parents thereafter provide their written consent to continue in the study; also termed “deferred” or “delayed” consent (21)]. Informed consent will be sought from the parent/guardian by the study team or medical officer as soon as practical.

Screening will start at the time when the medical team decides to treat a patient for sepsis as per the institutional sepsis pathway (Queensland Paediatric Statewide Sepsis Pathway, which is being used at all study sites) to enable a pragmatic screening entry point. The trial does not mandate specific physiological thresholds to assess shock, rather the point of enrolment reflects the decision by the treating clinician to start a sepsis treatment bundle. Clinicians are advised to give a first fluid bolus of 20 mL/kg (or 1,000 mL fluid bolus in patients >50 kg) as per SSC guidelines irrespective of any decisions regarding enrolment in the study. Clinicians can give this amount of fluid as one bolus or split into aliquots of smaller amounts of bolus fluid.

